| OBJECTIVES              | The aim of this research is to assess the efficacy of a low-carbohydrate (LC) diet in adults with type 1 diabetes (T1D). We will specifically set out to determine whether significant differences in T1D management outcomes exist between a LC diet and habitual diets higher in carbohydrate.                                                                                                                                                                                                                                                                                                                                                                                                  |
| PRIMARY HYPOTHESIS      | A low-carbohydrate (LC) diet will result in improved type 1 diabetes management compared to habitual diets higher in carbohydrates.                                                                                                                                                                                                                                                                                                                                                                                                                                                                                                                                                               |
| DESIGN                  | This is a 28-week single arm within-participant intervention study involving a 4-week control period, a 12-week intervention period and a 12-week follow-up.                                                                                                                                                                                                                                                                                                                                                                                                                                                                                                                                      |

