### **6.6.3 Self-monitoring ketones**

For safety purposes, participants will be required to self-monitor either urine or blood ketones regularly throughout the intervention period using their usual method(s) of measuring ketones. Participants will be required to measure their ketones at least twice per week, and more under certain circumstances (e.g., if feeling unwell) as per standard of care diabetes practices. To assist participants in doing this, the required amount of ketone test strips will be provided. A resource titled, 'Self-monitoring ketones' (Attachment 52) will be provided at the beginning of the intervention period to instruct participants on how and when to monitor for ketones, what level of ketones are and are not expected, and what to do if they are experiencing unexpected changes in blood or urine ketones. The resource will help participants understand that mild, controlled ketone readings are normal and expected with the LC dietary intervention. Nutritional ketosis is typically defined as a ketone reading within the range of 0.5–3.0 mmol/L [23] and should not be confused with DKA that is associated with a rapid increase in ketone levels typically 10 times the level observed with nutritional ketosis. Nevertheless, we are taking a conservative approach and advising participants to maintain ketones  $\leq 0.6$  mmol/L, as per usual standard diabetes practice. The resource, 'Self-monitoring ketones' (Attachment 52), includes guidelines on when to monitor for ketones, and what action to take if ketones are  $>0.6$  mmol/L. In brief, participants will be advised to refer to the resource titled 'Managing sick days' (Attachment 43) for more information. In any case, participants will be instructed to immediately inform [name] (study dietitian) of any instances where ketones are  $>0.6$  mmol/L and the case will be flagged with the study endocrinologist. The overseeing endocrinologist will then make a decision to either (a) continue as is or under certain condition (e.g., need to monitor

ketones once daily); (b) refer them to their nominated HCP or GP for independent review; or (c) refer them to the study diabetes educator or study physician for review. If [name] is unavailable, then [name] will be consulted to review the case. All cases referred will be documented and used to assess safety of the intervention in the data analysis and reporting.

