## **8. SAFETY CONSIDERATIONS**

### **8.1 Adverse event definitions**

For the purposes of this study, we will define adverse events as any incident that results in the participant requiring health care of which is directly attributed to involvement in the study. The expected risk of serious adverse events experienced as a result of the dietary intervention is low. However, participants will be advised to report details of any adverse events directly to the study dietitian or physician at any point during the control or intervention periods. In the unexpected case of a medical emergency, participants will be encouraged to dial 000 immediately and follow-up with researchers after medical treatment/assessment has been received and their condition is stable.

Adverse events have been described in detail in section 7.3 as potential risks that may be involved with participation in this research and include;

- Discomfort or infection(s) at the site of CGM/FGM, finger prick or venepuncture
- Increased frequency of hypoglycaemia
- Dehydration or sodium deficiency (e.g., headaches, muscle cramps, low energy, digestive discomfort)
- Diabetic ketoacidosis
- Psychological/emotional distress
- Social distress

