| Clinic visit 1
(start of week 0) | 
 
• Study schedule explained (Figure 1) and all visits/sessions for the control and intervention periods scheduled (inc. all sessions with study dietitian and study diabetes educator).
 
• Medical assessment scheduled, if necessary (i.e., for patients taking any medication(s) other than insulin).
 
• Equipment, demonstration and instructions provided for: 
 
- CGM/FGM device (sensor(s) and reader) (7-day monitoring)
 
- Insulin logbook (3-day monitoring)
 
- Diet record (participants will be shown how to download and use the Easy Diet Diary mobile app to accurately record their dietary intake) (3-day monitoring)
 
- Biological samples (Australian Clinical Labs request form provided, and nearest pathology collection centre to the participant identified)
 
 
 
• Control period educational resources discussed: 
 
○ general recommendations
 
○ NDSS fact sheet: Diabetes distress
 
○ preparing for your blood test
 
 
 
• Participants encouraged to report any adverse events throughout the study.
 
• Participants encouraged to maintain usual patterns of eating, activity and diabetes management.
 
 |

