| Clinic visit 2
(end of week 0)   | 
 
• Morning of clinic visit 2: Participants attend their nearest Australian Clinical Labs collection centre (fasted) to have biological samples taken. Participants instructed to have a meal and drink fluids after blood draw and before their clinic visit.
 
• Data collected (pre-control outcomes): 
 
- Return/upload CGM/FGM device/data
 
- Return/upload insulin logbook
 
- Return/upload diet record
 
- Anthropometric measurements taken (weight, height, waist circumference and blood pressure)
 
- Questionnaires completed (quality of life, physical activity and diet satisfaction)
 
 
 
• Participants encouraged to maintain usual patterns of eating, activity and diabetes management.
 
• Control period educational resources discussed: 
 
○ blood glucose monitoring
 
○ managing hypoglycaemia
 
○ managing sick days
 
 
 
                                                                                                                                                                                                                                                                                         |

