| Diet Session 0
(during week 2)   | 
 
• Telehealth call (Zoom) with study dietitian.
 
• Participants encouraged to maintain usual patterns of eating, activity and diabetes management.
 
• Control period educational resources provided: 
 
- carbohydrate counting
 
- reading food labels
 
 
 
                                                                                                                                                                                                                                                                                                                                                                                                                                                                                                                                                                                                                                                                                                                                                                                                                                                                                                                                                                               |

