| Clinic visit 4
(end of week 4)                                             | 
 
Morning of clinic visit 4: Participants attend their nearest Australian Clinical Labs collection centre (fasted) to have biological samples taken. Participants instructed to have a meal and drink fluids after blood draw and before their clinic visit.
 
Data collected (post-control/pre-intervention outcomes):               
 
Return/upload CGM/FGM device/data
 
Return/upload insulin logbook
 
Return/upload diet record
 
Anthropometric measurements taken (weight, height, waist circumference and blood pressure)
 
Questionnaires completed (quality of life, physical activity, diet satisfaction)
 
 
 
Participants encouraged to have a short break prior to diet session 1.
 
                                                                                                                                                                                                                                                                                                                                                                                                                                                                                                                                                                 |

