| Diet session 2
(during week 7)  | 
 
• Telehealth call (Zoom) with study dietitian.
 
• Review of dietary intake (collect diet history or review Easy Diet Diary tracking) and usual care blood glucose monitoring.
 
• Provide individualised dietary strategies for adhering to the intervention.
 
• Review understanding of information provided in diet session 1.
 
• Diet resources discussed in this session:               
 
- Dietary proteins
 
- Dietary fats
 
- Snack ideas
 
 
 
• Participants prompted to report any adverse events experienced (self-report) over previous 2 weeks (e.g., hypoglycaemia (<3.5 mmol/L), digestive issues, low energy levels, headaches, etc.)
 
• Participants encouraged to follow-up with their nominated healthcare professional to discuss insulin management.
 
                                                                                                                                                                                                                                                                                                                                          |

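### Table 1 prompts for symptoms at five diet-period sessions and at no control-period contact, so any control-versus-diet comparison of self-reported symptoms would be biased against the diet

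*Protocol*

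**What the plan says.** The Synopsis describes a single-arm, within-participant study "involving a 4-week control period, a 12-week intervention period and a 12-week follow-up". Section 8.1 advises participants to report adverse events themselves "at any point during the control or intervention periods".

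Table 1 (section 15) sets out what happens at each contact.

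- **Control period.** Clinic visit 1 carries a general invitation: "Participants encouraged to report any adverse events throughout the study". Clinic visits 2, 3 and 4 list no adverse-event item. Neither does Diet Session 0 in week 2, which lists two education resources and the reminder "Participants encouraged to maintain usual patterns of eating, activity and diabetes management".
- **Intervention period.** Diet session 1 repeats the general invitation. Diet sessions 2, 3, 5 and 6 carry the active item "Participants prompted to report any adverse events experienced (self-report) over previous 2 weeks", followed by examples such as hypoglycaemia, digestive issues, low energy and headaches. Diet session 4 also collects actively over the past two weeks, but asks about side effects rather than adverse events.

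The examples vary too: sessions 2 to 4 name hypoglycaemia below 3.5 mmol/L, and sessions 5 and 6 name severe hypoglycaemia.

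**The concern.** Asking someone about headaches, tiredness or gut upset over the last fortnight is expected to bring out more reports than leaving them to volunteer. Here the first method is used only on the diet and the second is all that the control period has. The named symptoms are common and non-specific, so a count on the diet means little without knowing how often the same people report them on their usual diet.

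The protocol's safety definitions lean on that knowledge. Under section 8.1 an adverse event must be attributable to taking part, and the listed risks include symptoms of dehydration or sodium deficiency of just this kind. Under section 8.2 the study physician may respond to an event by changing or stopping the study. What is at stake is the reading of tolerability, not the primary outcome. Symptoms not asked about in the control weeks cannot be recovered by any later analysis plan.

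**Working it through.** The protocol gives no adverse-event rate or comparison to reproduce, so the check is a count of Table 1 followed by an illustration on stated assumptions.

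**Step 1. Active collections by contact (Table 1).**

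| Contact | Adverse-event item |
|---|---|
| Clinic visit 1 (start of week 0) | general invitation |
| Clinic visit 2 (end of week 0) | none |
| Diet Session 0 (week 2) | none |
| Clinic visit 3 (start of week 4) | none |
| Clinic visit 4 (end of week 4) | none |
| Diet session 1 (end of week 4) | general invitation |
| Diet sessions 2, 3, 5, 6 (weeks 7, 9, 13, start of 16) | active, two-week recall |
| Diet session 4 (week 11) | active, two-week recall, worded as side effects |

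Active collections: control 0, intervention 4 + 1 = 5.

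**Step 2. Weeks under prompted recall.** Intervention: 5 × 2 = 10 of 12 weeks, approximately. Control: 0 × 2 = 0 of 4 weeks.

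**Step 3. Direction of the bias.** Let the true weekly symptom rate be the same in both periods. Let *p* be the share of symptoms recorded in prompted weeks, *s* the share recorded spontaneously, and *c* = 10/12 the prompted share of diet weeks. The apparent diet-to-control ratio of weekly rates is

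RR = [*c*·*p* + (1 − *c*)·*s*] / *s*,

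which exceeds 1 whenever *p* > *s*.

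**Step 4. Illustration only.** Neither *p* nor *s* is in the documents. Assume *p* from 0.8 to 1.0 and *s* from 0.3 to 0.7.

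- Smallest: *p* = 0.8, *s* = 0.7 gives (0.667 + 0.117)/0.7 = 1.12.
- Largest: *p* = 1.0, *s* = 0.3 gives (0.833 + 0.050)/0.3 = 2.94.

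On these assumptions the ratio runs from about 1.1 to 2.9 with no diet effect. Other assumptions give other ranges; only the direction is firm.

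**Step 5. Raw counts.** The periods last 12 and 4 weeks, so unadjusted counts would differ by a further 12/4 = 3-fold from exposure alone.

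**Step 6. With matched prompts.** Two prompts at Diet Session 0 and Clinic visit 4 cover 2 × 2 = 4 of 4 control weeks, approximately.

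**The case against.** The strongest reply is that the protocol never plans the comparison. Its outcomes (section 9) include no symptom or adverse-event rate, and the stated safety use in sections 6.6.3, 7.3.2 and 7.3.4 is of documented referrals. Section 8.1 also limits adverse events to incidents that need health care, which many prompted headaches or spells of low energy would not. This stands, and it limits the point to any comparison or attribution that someone later makes. It does not remove the point, because attribution is built into the definition and the control period is the only baseline there is.

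A second reply is that the control period does have surveillance. Part of this stands: hypoglycaemia frequency comes from seven-day sensor data collected alike at all three time-points (sections 9 and 9.2), so it is not affected. The fortnightly review in section 7.3.2 covers glucose data, not symptoms. Section 7.3.3 has the dietitian check sodium-related symptoms at every fortnightly diet session, but the Synopsis counts six such sessions, Diet session 1 in Table 1 also refers to six, and Table 1 lists no symptom check at Diet Session 0. At best the text is unclear.

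Third, matched prompts would not make an unblinded, sequential single-arm study able to prove that the diet causes a symptom. True; they remove one avoidable source of bias and leave the rest.

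Three stronger readings are tempting but unsupported.

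- A reader might infer that the diet's symptom burden will be overstated. Prompting does not inflate what happens on the diet; it leaves the control period under-recorded, so only the contrast is biased.
- A reader might infer that the collection method switches on the day the diet starts. Diet session 1 carries the same invitation as Clinic visit 1, and the first prompt comes in week 7.
- A reader might count ketone testing, required "regularly throughout the intervention period using their usual method(s) of measuring ketones", as a second asymmetry to be matched. It is safety monitoring for the diet and not an outcome, and adding it would alter a period meant to keep usual management.

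**Conclusion.** The point holds as a defect in data collection: five active collections in the intervention period against none in the control period, or about 10 of 12 weeks against 0 of 4 under prompted recall. These figures rest on Table 1 alone, taking each item as a full two-week look-back. Any control-versus-diet comparison of non-specific self-reported symptoms would be biased against the diet, assuming only that a prompt captures more than spontaneous reporting does. The amount cannot be computed from the documents, and the range of 1.1 to 2.9 should not be cited as an estimate. The primary outcome and sensor-derived hypoglycaemia frequency are untouched. This is an inexpensive improvement to safety interpretation, worth making before enrolment because the missing control data cannot be supplied afterwards.

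**What to change.** In Table 1, use one identically worded symptom prompt, with the same examples, two-week recall and REDCap form, at:

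- Diet Session 0 (week 2);
- Clinic visit 4 (end of week 4), completed before Diet session 1 begins;
- Diet sessions 2 to 6, replacing the present varying wording, including the side-effects wording at session 4 and the change of hypoglycaemia example at sessions 5 and 6.

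Report each symptom per participant-week of prompted recall, by period. State in section 7.3.3 whether its symptom check at each diet session includes Diet Session 0, so that it agrees with Table 1.

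If the control-period prompts are not added, state in the protocol that self-reported symptoms will not be compared between periods.

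The cost is a few minutes at two contacts that already exist: at most 2 × 20 = 40 extra prompts if all 20 participants enrol.
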